### Concealment mechanism {16b}

Each physician and non-physician name will be blindly placed into an envelope that contains a computer-generated random number.

### Implementation {16c}

The allocation sequence is generated by the computer, and the concealment is performed by a member of the research team. After study investigators open the sealed envelope, they can enroll the participants and assign them to interventions.

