**Methods:**

A randomized controlled trial will be conducted in two large academic medical centers. Two hundred ICU clinicians will be recruited with target enrollment of 100 physicians and 100 non-physicians (nurses, pharmacists, therapists). Participants must have worked in the ICU for the equivalent of at least 1 full time work week in the preceding 4 weeks. Enrolled subjects will be randomized to virtually attend biweekly debriefing sessions facilitated by a psychotherapist for 3 months or to a control arm without sessions. Our debriefs are modeled after Death Cafés, which are informal discussions focusing on death, dying, loss, grief, and illness. These sessions allow for reflection on distressing events and offer community and collaboration among hospital employees outside of work.

The primary outcome is clinician burnout as measured by the Maslach Burnout Inventory (MBI) Score. Secondary outcomes include depression and anxiety, as measured by the Patient Health Questionnaire 8 (PHQ-8) and Generalized Anxiety Disorder 7-item scale (GAD-7), respectively. Questionnaires will be administered prior to the intervention, at 1 month, at 3 months, and at 6 months after enrollment. These values will be compared between groups temporally. Qualitative feedback will also be collected and analyzed.

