### Trial design {8}

STOPTHEBURN is a parallel group randomized controlled trial with a 1:1 allocation ratio.

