## Assignment of interventions: allocation

### Sequence generation {16a}

Randomization will utilize an online random number generator and will be performed in pairs such that each time a physician is randomized to a study arm, a non-physician will also be randomized to that study arm for balance.

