### Participant timeline {13}

Subjects in the Death Café arm of the study will participate in 4 debriefing sessions over 3 months from the time of enrollment. Surveys will be administered by email to participants in both arms of the study prior to the intervention, at 1 month, at 3 months, and at 6 months after enrollment. Figures 1 and 2 demonstrate the flow of participants through the study.

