### Recruitment {15}

Recruitment will be performed in person at each ICU site and electronically via email to employee listservs on a biweekly basis until target enrollment is reached. Recruitment will involve screening for eligibility, providing potential participants with information about the study, and obtaining informed consent. Participants will be offered compensation for completion of a minimum number of study procedures. This will be $140 for completion of the Death Café study arm and $40 for the control arm.

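### Implementation {16c} has the allocation envelope opened before enrolment, against the abstract, and neither entry of both pair members nor the baseline survey is fixed before the arm is revealed

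*Protocol article*

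**What the plan says.** All references are to the protocol article.

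- **Order of entry.** Implementation {16c}: "After study investigators open the sealed envelope, they can enroll the participants and assign them to interventions". The same section says that "the concealment is performed by a member of the research team". The abstract (Methods) has the reverse order: "Enrolled subjects will be randomized to virtually attend biweekly debriefing sessions".
- **Envelope.** Concealment mechanism {16b}: "Each physician and non-physician name will be blindly placed into an envelope that contains a computer-generated random number".
- **Pairing.** Sequence generation {16a}: "each time a physician is randomized to a study arm, a non-physician will also be randomized to that study arm for balance".
- **Consent.** Recruitment {15}: "Recruitment will involve screening for eligibility, providing potential participants with information about the study, and obtaining informed consent". The consent section {26a} adds that the procedures of both arms are explained. Neither section places consent relative to the opening of the envelope.
- **Baseline survey.** Participant timeline {13}: "Surveys will be administered by email to participants in both arms of the study prior to the intervention". The abstract also ties the first survey to the start of the intervention. Outcomes {12} places it at enrolment.
- **Knowledge of the arm.** Participants are told their allocation ({17a}) and enter their own survey data online ({18a}). Payment on completion is $140 in the Death Café arm and $40 in the control arm ({15}, {18b}).

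**The concern.** Allocation concealment protects the comparison only if the decision to enter a person is final before anyone involved in that decision can see the arm. A site following {16c} to the letter would see the arm first. The pairing rule opens a second route: once a physician's arm is known, so is the arm of the non-physician who goes with it. Recruitment runs in biweekly rounds ({10}, {15}), so the two need not arrive together.

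Several features of this trial give people a reason to act on such knowledge. Study investigators obtain consent, part of recruitment is face to face, one arm asks for evening sessions, and payment differs by arm. The Challenges section expects overwhelmed staff to be reluctant to take on a time-consuming intervention, and it relies on randomisation to deal with confounders. That reliance fails if entry depends on the arm. Neither the intention-to-treat analysis ({20a}) nor the masked statistician ({17a}) can undo selection that happened before entry.

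The baseline is a separate matter. A self-reported burnout, depression or anxiety score given after learning the arm may reflect relief or disappointment, and whether the survey is completed at all may depend on the arm. This is mainly expectation or reporting bias, with some arm-dependent non-completion, rather than selection bias in the strict sense. It matters because {20a} compares the first survey with the 3- and 6-month scores.

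**Working it through.** The plan gives no figure on this point to reproduce. The check compares the sections and makes one count.

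**1. Order of enrolment and allocation.**
- Abstract: enrolled, then randomised.
- {16b}: names go into the envelope with the random number, so people are identified before it is opened.
- {16c}: envelope opened, then enrolment and assignment.

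The first and third cannot both hold if enrolment has the same meaning in each. The second fits the first better than the third, but being named in an envelope is not the same as having consented and been entered.

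**2. Foreseeable allocations from pairing.**
Inputs: 200 participants, about 100 physicians and 100 non-physicians (Sample size {14}); one shared arm per pair ({16a}). This gives about 100 pairs and 100 second members.

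Let *s* be the share of pairs in which the second member is entered after the first member's arm is known. Then

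foreseeable allocations = 100 × *s*, out of 200.

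- *s* = 0 (both entered first, arms revealed together): 0 of 200, or 0%.
- *s* = 0.5: 100 × 0.5 = 50 of 200, or 25%.
- *s* = 1 (always one after the other): 100 of 200, or 50%.

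The documents do not give *s*, so the range is 0 to 100 of 200.

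**3. Timing of the baseline survey.**
- Before the intervention (abstract, {13}): this permits completion between notification of the arm and the first session.
- At enrolment ({12}): under the abstract's order this could precede allocation; under {16c} it follows the opening of the envelope.

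Neither wording requires the survey to be in before allocation, and under {16c} the second wording puts it afterwards.

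**4. Two side issues, checked for size.**
- Chance imbalance. The design is a "parallel group randomized controlled trial with a 1:1 allocation ratio". Simple randomisation of 100 pairs gives a 95% range of 40 to 60 pairs per arm (Binomial(100, 0.5)). At 60/40, efficiency relative to an even split is 4 × 0.6 × 0.4 = 0.96.
- Pair as randomised unit. The design effect for pairs is 1 + ICC. The documents give no ICC; assuming 0 to 0.05 gives 1.00 to 1.05, an effective sample size of 200 down to 200/1.05 = 190.5.

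**The case against.** The strongest reply is that {16c} is loosely worded. Read with the rest, the intended sequence may be recruitment and consent, names sealed, envelope opened, people assigned, with enrolling in {16c} meaning no more than registering someone in an arm. Names are said to be placed blindly, and consent covers both arms. If one envelope holds both names of a pair, both identities are fixed before opening. The two figures, a flow diagram and a SPIRIT timeline, are not reproduced in the text available and may show the order. A journal article may also leave procedural detail to the full protocol.

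Much of this stands as an account of what was probably meant, and it is why the foreseeable share is given as a range starting at zero. It does not remove the point. The article states an order rather than omitting one, and that order conflicts with its abstract. No section says that consent, enrolment and the baseline survey are complete before opening. A person already named in an envelope but not yet committed could still decline once the arm is known.

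A reader might go further in three ways that the documents do not support:

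- *All 200 allocations are known before entry.* This needs the literal reading of {16c}, which the abstract contradicts and {16b} does not fit.
- *The 1:1 ratio is not delivered.* Simple randomisation is 1:1 in expectation, the article does not say that the list is unrestricted, and even a 60/40 split loses only 4% efficiency.
- *Randomising pairs does material harm to the analysis.* Nothing says that pair members share a unit or shift, and the assumed ICC range shows little loss.

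**Conclusion.** The point holds as a contradiction in the stated procedure, together with two steps not fixed in time. {16c} and the abstract disagree on whether enrolment comes before or after the arm is seen. The pairing rule leaves between 0 and 100 of 200 allocations foreseeable, assuming about 100 complete pairs and depending on whether members are entered together or in turn. The baseline survey is not required before allocation, in a trial where participants know their arm and report their own outcomes.

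The documents allow arm-aware entry and an arm-aware baseline; they do not show that either will happen, and the size of any resulting bias cannot be computed from them. The point still deserves correction before recruitment, because the remedy costs almost nothing and biased entry cannot be repaired in the analysis.

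**What to change.** Reconcile the abstract, {12}, {13} and {16a} to {16c} so that all state one order: eligibility confirmed; consent given and participant enrolled; baseline survey submitted in REDCap; allocation revealed.

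For the pairing rule, choose one of the following:

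- Keep it, and state that both members must complete all the steps above before the envelope is opened and that both allocations are revealed together.
- Replace it with individual allocation from a concealed list stratified by role (physician or non-physician). This keeps the role balance that {16a} seeks without tying two people to one arm.

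Varying block sizes or stratifying by hospital would be a design preference and is not needed to correct this point.

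The cost is a short amendment, plus preparing and loading a list if the second option is chosen. REDCap is already used for the surveys, and no extra participants are needed. Waiting for both pair members may slightly delay some entries under the first option. If recruitment has already started, record the order actually used and report it with the results.

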## Assignment of interventions: blinding

### Who will be blinded {17a}

Trial participants will be notified of their randomly allocated condition (Death Café intervention group or control group) and the associated study procedures. The psychotherapists hosting the Death Cafés cannot be blinded to group allocation as they will be leading the intervention. Members of the research team will not be blinded to the assigned arm of the study if they are directly assisting with coordination of the Death Café debriefing sessions. Other members of the study team who are not hosting or coordinating these sessions will be blinded to each participant’s group allocation. An independent statistician will conduct data analysis and will be blinded to the nature of each group undergoing analysis (will be labeled as “A” and “B”).

### Procedure for unblinding if needed {17b}

Unblinding will not be performed unless requested by the Tulane University Institutional Review Board, which is the regulatory committee that approved this study.

## Interventions

### Explanation for the choice of comparators {6b}

In order to test the study hypothesis, psychometric outcomes of those who participate in Death Café debriefing interventions will be compared with those not participating in debriefing.

### Intervention description {11a}

In the intervention arm, participants will be asked to participate in at least 4 Death Café debriefing sessions over 3 months hosted by one of our two psychotherapists (RH and NR) [7]. These sessions will occur virtually through a teleconferencing platform in the early evening (after daytime work hours) in an effort to optimize attendance. Subjects will be notified of the date, time, location, and what to expect in the session in advance via the contact information provided on their consent form.

### Criteria for discontinuing or modifying allocated interventions {11b}

Participants may request to discontinue participation in the study at any time.

### Strategies to improve adherence to interventions {11c}

RH and NR will lead the Death Café debriefing sessions virtually in a manner consistent with previous work [7]. This format, as well as the full study protocol, will be reviewed quarterly at investigator meetings. Death Café debriefing sessions will be randomly attended by other study investigators throughout the course of the study to monitor consistency of adherence to the Death Café intervention structure.

### Relevant concomitant care permitted or prohibited during the trial {11d}

Participants will be permitted to engage in concomitant care as each deems personally necessary for burnout, depression, or anxiety symptoms during the trial.

### Provisions for post-trial care {30}

If subjects experience distress, they can contact the trained psychotherapists on our study team (RH and NR) for triage to appropriate mental health care. Their contact information will be provided to subjects in the consent document. For acute suicidal emergencies, participants will consent to a plan to call 9-1-1 or present to the nearest emergency room.

### Outcomes {12}

The primary outcome of the study is employee burnout as measured by the Maslach Burnout Inventory (MBI) Score*.* Mean total MBI score and mean subscores will be calculated. Presence of burnout is defined by high values of depersonalization (> 10/30) and emotional exhaustion (> 27/54) with low values for personal accomplishment (< 33/48) as defined in previous studies [40].

Secondary outcomes include employee depression and employee anxiety. These will be determined by the Patient Health Questionnaire 8 (PHQ-8) and Generalized Anxiety Disorder 7-item scale (GAD-7) which evaluate frequency of symptoms over the last 2 weeks. Scores of 10 or higher on these assessments are considered to indicate clinically significant depression or anxiety, respectively [41–43].

Scores will be compared between groups and analyzed from the beginning to the end of the intervention period (at enrollment, 1 month, 3 months, and 6 months after enrollment). The surveys will also include free text response options allowing participants in the intervention arm to comment on strengths and areas for improvement of the intervention.

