## Introduction

### Background and rationale {6a}

Burnout is an occupational syndrome characterized by emotional exhaustion, distant or indifferent attitude toward work, and reduced sense of personal accomplishment [1]. It affects physicians and ancillary healthcare providers on a national scale [2–7]. The prevalence of burnout is as high as 60% in hospital employees at one of our institutions, an urban, academic, Level One trauma center [7]. Those caring for critically ill patients are especially susceptible to burnout due to features specific to the intensive care unit (ICU) such as high patient morbidity and mortality, long hours, and regular encounters with trauma and ethical issues. These experiences lead to moral distress and compassion fatigue [5, 8–12].

Burnout not only impacts the ability to enjoy work but also may lead to depression, posttraumatic stress disorder, substance abuse disorder, and suicidality [4, 5, 13, 14]. It can increase the rate of job turnover, leading to caregiver shortages [5, 10]. Most significantly, burnout is known to contribute to patient safety events [5, 15]. Physicians and nurses with burnout are more likely to make medical errors, deliver a lower quality of care, and communicate poorly with their patients [4, 14, 16–28]. Burnout is associated with higher 30-day mortality and rates of hospital-acquired infections [5].

In spite of the growing awareness of the consequences of burnout, interventions to prevent or address burnout are sparse in the literature [5, 15, 29]. Most interventions to date have focused on reduction in work hours, development of wellness curricula, and mindfulness promotion [29–32]. Preliminary studies suggest that debriefing opportunities may reduce burnout through enhancement of social support and interprofessional collaboration [33–37].

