### Sample size {14}

The target enrollment is 200 ICU employees, of which we expect approximately 100 physicians and 100 non-physicians (nurses and therapists) in the study. This is based on a power analysis we performed for the ability to detect 20% reduction in burnout prevalence or a change of greater than 4 in mean Maslach Burnout Inventory Score (power of 0.8, alpha of 0.05).

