## Statistical methods

### Statistical methods for primary and secondary outcomes {20a}

Descriptive statistics will be reported for participant recruitment, study dropout, and engagement with the intervention. Baseline characteristics for each group will be reported. All analyses will be conducted on an intention-to-treat basis.

Unadjusted associations between independent risk factors (i.e., age, gender, and presence of primary or secondary outcome) will be assessed using Student’s *t* test or Wilcoxon rank sum test for continuous variables and a chi-square test for categorical variables. These risk factors and scores will be compared between the intervention and control group as well as analyzed from the beginning to the end of the intervention period (pre-survey compared to 3-month and 6-month scores). Mixed model regression will also be utilized to analyze differences between groups. Qualitative thematic analysis of free text response feedback regarding the intervention will be performed. All analyses will be performed using SAS Enterprise Guide 5.1 (SAS Institute, Inc., Cary, NC).

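### The primary MBI variable, time point and test are not fixed, so the protocol text does not hold type I error at its stated 0.05

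*Protocol article*

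**What the plan says.** **Variable.** Outcomes {12} names burnout measured by the MBI as primary. It says a mean total and mean subscores will be calculated, and defines burnout as present when depersonalization and emotional exhaustion are high and personal accomplishment is low. That gives four continuous quantities and one binary one, with no order among them. Objectives {7} states the hypothesis in terms of burnout rates. Sample size {14} refers to the "ability to detect 20% reduction in burnout prevalence or a change of greater than 4 in mean Maslach Burnout Inventory Score", with "power of 0.8, alpha of 0.05".

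**Time point.** Outcomes {12}: "Scores will be compared between groups and analyzed from the beginning to the end of the intervention period". The bracket that follows lists enrollment, 1, 3 and 6 months. Intervention description {11a} and Participant timeline {13} place the debriefing sessions within 3 months. Statistical methods {20a} describes the analysis over the intervention period as "pre-survey compared to 3-month and 6-month scores".

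**Test.** {20a} gives the t test or Wilcoxon test for continuous variables and chi-square for categorical ones, and adds that mixed model regression will be used as well. None is called the primary test.

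**The concern.** A stated alpha of 0.05 has meaning only when attached to a defined comparison. Here three choices stay open: which MBI quantity, which visit and which test.

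The candidate measures can disagree. A shift in mean score need not move people across all three cut-offs, and the reverse is also possible. The article does not say how a total combines subscores that point in opposite directions in its own burnout definition.

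With these choices open, the result called primary could be selected after the data are seen without departing from the text. Participants know their arm and report their own outcomes, which makes a comparison fixed in advance more valuable. The Implications section says hospital systems should consider adopting the sessions if they prove effective, so the claim has consequences.

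**Working it through.** **1. The plan's own figure.** "The target enrollment is 200 ICU employees", and the design is a "parallel group randomized controlled trial with a 1:1 allocation ratio", so 100 per arm. Alpha 0.05 and power 0.8 are stated; two-sided is assumed. Background {6a} says "The prevalence of burnout is as high as 60% in hospital employees at one of our institutions"; this is not given as a power input, so using 60% is an assumption. Reading 20% as absolute points is another.

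n per arm = [z(0.975)·√(2p̄(1−p̄)) + z(0.80)·√(p₁(1−p₁)+p₂(1−p₂))]² / (p₁−p₂)²

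With p₁ = 0.60, p₂ = 0.40, p̄ = 0.50: [1.960×0.7071 + 0.8416×0.6928]² / 0.04 = 1.969² / 0.04 = 96.9, so 97 per arm and 194 in total. Power at 100 per arm is 81.2%.

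- From 50% to 30%: 186 in total.
- A relative 20% reduction from 60% (to 48%): 540 in total.
- Mean-score leg: n = 2×(1.960+0.8416)²×SD²/4². No SD is stated. SD 10 gives 2×7.849×100/16 = 98.1, so 99 per arm and 198 in total; SD 12 would need 284. This leg can only be back-solved.

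Prevalence alone therefore roughly accounts for 200, using a background figure in the article.

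**2. What the sections fix.**

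| Element | Objectives {7} | Outcomes {12} | Sample size {14} | Statistical methods {20a} |
|---|---|---|---|---|
| Variable | burnout rates | total, 3 subscores, binary | prevalence or mean score | scores, unspecified |
| Visit | none | 1, 3 and 6 months | none | 3 and 6 months for change from the pre-survey |
| Test | none | none | none | t/Wilcoxon, chi-square, also mixed model |

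No row settles on one entry. Outcomes {12} also counts 6 months in an intervention period that {11a} and {13} limit to 3 months.

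**3. Error rate if any significant result could be called primary.** For k independent tests at 0.05 the rate is 1 − 0.95^k, an upper guide when tests are positively correlated. For two tests this is 1 − 0.9025 = 9.8%; for fifteen it is 53.7%.

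For correlated tests, 6,000 null trials per setting were simulated with 100 per arm, t tests for scores and a chi-square-type test for the binary measure. Assumptions:

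- between-subscore correlation 0.3 to 0.7, with personal accomplishment at 0.6 times that;
- between-visit correlation 0.4 to 0.8;
- means (SD) of 26 (12) for emotional exhaustion, 9.5 (6.5) for depersonalization and 36 (7) for personal accomplishment, which is reversed in the total.

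| Tests from which one could be picked | Independent | Correlated (simulated) |
|---|---|---|
| One measure, one visit | 5% | 5.0-5.6% |
| Total and prevalence, one visit | 9.8% | 8.8-9.4% |
| Total, three visits | 14.3% | 10.0-13.0% |
| Five measures, one visit | 22.6% | 15.3-18.1% |
| Total and prevalence, three visits | 26.5% | 19.0-23.6% |
| Five measures, 3 and 6 months | 40.1% | 24.1-31.3% |
| Five measures, three visits | 53.7% | 29.9-42.4% |

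The assumed scores put simulated burnout prevalence at 11-18%, well under the 60% background figure, so the rows that include prevalence are approximate. The two-test row is bounded whatever the correlation: it cannot exceed 2 × 5% = 10%.

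**The case against.** A reader might infer that the plan has an either-or success rule and fifteen co-primary tests, so that its false-positive rate is far above 5%. The documents do not support that.

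- The word joining the two effects in Sample size {14} describes what the trial can detect. No section says the trial succeeds if either is significant.
- Outcomes {12} says the total and subscores will be calculated; it does not make each a co-primary test. Fifteen is an upper count of what could be compared.
- Statistical methods {20a} also offers a mixed model, and {20c} relies on it for missing data. One mixed-model test on one measure would hold 5%.
- The hypothesis and the first part of the power statement both concern prevalence, so the text leans toward one measure.
- The bracket about 3 and 6 months in {20a} attaches to the change-over-time analysis. It does not show that between-arm comparisons omit month 1.

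These points stand, and they make the error rates above conditional. They do not close the gap: prevalence is never designated primary, no visit is chosen, and the mixed model is an addition to the other tests.

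It can also be said that this is called a pilot study and that multiplicity rules usually sit in an analysis plan, which is not shown. The second point excuses the absence of a multiplicity procedure. It does not excuse leaving the primary variable and visit open, which a protocol should settle, or sections that disagree. The pilot label carries limited weight when the article also anticipates hospital uptake.

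**Conclusion.** The point holds as a failure to fix the primary comparison. The protocol does not settle the variable, visit or test, and it puts two effect measures under one alpha of 0.05. Type I error is therefore not controlled by the text at the stated level.

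The realised rate cannot be derived from the document. It is 5% if one comparison is fixed before the data are seen. If selection were allowed, it would be about 9% for the two measures in the power statement at one visit, and roughly 30-40% for all five measures at three visits. Those figures rest on separate two-sample tests and on assumed correlations, means and SDs.

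**What to change.** Name one primary comparison that agrees with Objectives {7} and Sample size {14}. One example is the between-arm difference in burnout prevalence, by the definition in Outcomes {12}, at 3 months, estimated from the mixed model (in a form suited to a binary outcome) at two-sided 0.05. Then:

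- declare the total MBI, the subscores and the 1- and 6-month visits secondary;
- reduce the power statement to that one measure, giving the control prevalence and saying whether 20% is absolute or relative;
- align the visits and the intervention-period wording in {12} and {20a} with {11a} and {13}.

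Prevalence is the more natural choice than a subscore such as emotional exhaustion, which appears in neither the hypothesis nor the power statement.

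**Cost.** Protocol wording and a registry update, best made before enrollment. With 60% to 40%, 194 are needed, so 200 suffices before dropout, with a margin of only six. The article does not say whether the 60% figure uses the same three-part definition; the authors should confirm this. The small downside is that a result on another MBI measure or visit can no longer be claimed as primary.

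Keeping prevalence and mean score as joint primaries at one visit would cost more. At 0.025 each, the prevalence comparison needs [2.241×0.7071 + 0.8416×0.6928]² / 0.04 = 2.168² / 0.04 = 117.5, so 118 per arm and 236 in total. With 200 participants its power would be 72.5%.
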